## Abstract

**Introduction:**

Whiplash-associated disorder grade 2 (WAD2) is characterised by musculoskeletal pain/tenderness but no apparent nerve injury. However, studies have found clinical features indicative of neuropathy and neuropathic pain. These studies may indicate peripheral nerve inflammation, since preclinical neuritis models found mechanical sensitivity in inflamed, intact nociceptors. The primary aim of this study is to establish the contribution of peripheral neuroinflammation to WAD2 and its role in prognosis. Participants will be invited to participate in a sub-study investigating the contribution of cutaneous small fibre pathology to WAD2.

**Methods and analysis:**

115 participants within 1 month following whiplash injury and 34 healthy control participants will be recruited and complete validated questionnaires for pain, function and psychological factors. Data collection will take place at the Universities of Sussex and Oxford, UK. Clinical examination, quantitative sensory testing and blood samples will be undertaken. MRI scans using T2-weighted and diffusion tensor images of the brachial plexus and wrist will determine nerve inflammation and nerve structural changes. Skin biopsies from a substudy will determine structural integrity of dermal and intraepidermal nerve fibres. At 6 months, we will evaluate recovery using Neck Disability Index and a self-rated global recovery question and repeat the outcome measures. Regression analysis will identify differences in MRI parameters, clinical tests and skin biopsies between participants with WAD2 and age/gender-matched controls. Linear and logistic regression analyses will assess if nerve inflammation (MRI parameters) predicts poor outcome. Mixed effects modelling will compare MRI and clinical measures between recovered and non-recovered participants over time.

**Ethics and dissemination:**

Ethical approval was received from London-Brighton and Sussex Research Ethics Committee (20/PR/0625) and South Central—Oxford C Ethics Committee (18/SC/0263). Written informed consent will be obtained from participants prior to participation in the study. Results will be disseminated through publications in peer-reviewed journals, presentations at national/international conferences and social media.

**Trial registration number:**

NCT04940923.

Strengths and limitations of this studyThis study will evaluate the contribution of peripheral nerve inflammation to whiplash-associated disorder grade 2 and its role in prognosis.The design will enable us to understand if simple clinical tests can be used to identify nerve inflammation.One potential limitation of a two-site study can be variation in data collection between sites, although regular meetings and site visits have been put in place to minimise this.The use of different scanners could result in non-homogenous data sets; however, identical scanner types are being used, which should reduce the impact of this potential issue.It is not possible to blind the examiner to the status of patients versus healthy control participants, which may influence digital nerve palpation; therefore, care will be taken to ensure similar pressures are applied to both groups where possible.

## Introduction

Whiplash injury sustained by a motor vehicle collision can cause significant long-term pain and disability. In the UK, economic costs are as high as £3 billion per year mostly due to healthcare costs.^1^ Most whiplash cases are considered whiplash-associated disorder grade 2 (WAD2), as defined by the Quebec Task Force Classification system.^2^ WAD2 refers to musculoskeletal pain and tenderness but with no frank nerve injury identified during routine clinical testing (eg, electrodiagnostic testing, neurological bedside testing). Approximately 50% of the people with WAD2 develop chronic symptoms that frequently persist for more than 5 years.^3 4^ Although a limited number of prognostic factors have been identified,^5^ they do not indicate a site of tissue pathology. This lack of understanding of the underlying pathophysiology likely explains why treatments for this condition are relatively ineffective.^6 7^ Despite the absence of a detectable nerve injury on routine clinical testing, many of the clinical features of WAD2 indicate a syndrome that is neuropathic in nature, such as reduced vibration thresholds, cutaneous thermal hypoaesthesia and cutaneous hypersensitivities to tactile and thermal stimuli distal to the site of injury.^3 8–14^ Furthermore, clinical tests of nerve trunk mechanical sensitivity, such as palpating over upper limb peripheral nerve trunks and positioning the upper limb in postures that increases the tension in the brachial plexus and median nerve (the upper limb neurodynamic test-1; ULNT1), provoke symptoms in many patients.^8 9 14^ Based on these findings, we propose that some people diagnosed with WAD2 may have an undetected nerve pathology, such as peripheral neuroinflammation, which could be a cause of chronicity. Consistent with a role for neuroinflammation, animals with a localised neuritis develop tactile and thermal-evoked cutaneous hypersensitivities in the absence of axonal degeneration.^15–17^ Of note, intact nociceptive axons become mechanically sensitive responding to pressure and stretch,^17–20^ similar to the neural mechanosensitivity observed in people with WAD2.

Magnetic resonance (MR) neurography has gained increasing interest in the diagnosis of peripheral nerve pathology.^21–23^ An increased signal intensity on T2-weighted sequences is considered an imaging correlate of the intraneural oedema associated with peripheral neuroinflammation. Accordingly, T2-weighted signal is increased in animal models of neuroinflammation,^24 25^ and correlates positively with histological findings of inflammation.^25^ Using T2-weighted MR neurography in a group of patients with chronic WAD2, we have identified increased signal intensity in the cervical nerve roots and the median nerve at the carpal tunnel, indicative of peripheral neuroinflammation.^9^ In addition to T2-weighted MR neurography, diffusion tensor imaging (DTI) has recently been employed to examine the microstructural integrity of peripheral nerves.^26 27^ DTI evaluates the diffusivity of water molecules within nerves, which can provide information on the integrity of axons and myelin sheaths,^28 29^ as well as intraneural oedema.^30^

In addition to neuroinflammation and functional changes to the nervous system, there is also some evidence for the presence of structural nerve pathology in patients with WAD2. This is apparent by a decreased intraepidermal nerve fibre density in the index finger in patients with chronic WAD2.^14^ It currently remains unknown whether such small fibre degeneration is already apparent in the early stages after injury and whether it predicts outcome.

The main aim of this study is to establish the contribution of peripheral nerve pathology to WAD2 and its role in prognosis. Our primary focus is on peripheral neuroinflammation, which we will evaluate using a detailed examination, including MRI of the brachial plexus and distal nerve trunks, blood markers and clinical tests of nerve trunk mechanical sensitivity. Additionally, recruited participants will be invited to participate in a substudy that will use skin biopsies to establish the contribution of cutaneous nerve fibre pathology to WAD2. Our results will advance our understanding of the pathology underlying WAD2 and may identify factors that predict the development of persistent symptoms.

## Methods and analysis

### Objectives

The first objective of this study is to determine the presence of peripheral neuroinflammation during the acute stage following a WAD2 injury. This objective will use MRI to assess the extent of peripheral neuroinflammation and nerve microstructure in a cross-section of patients within 4 weeks of injury and healthy controls. The second objective will determine whether the presence of peripheral neuroinflammation in the acute stage can predict patient recovery status at 6 months. The third objective will determine the course of peripheral neuroinflammation from the acute to chronic stages of a WAD2 injury. For this objective, we will examine changes in MRI measures and clinical tests from baseline to 6 months in both recovered and non-recovered patients. The fourth objective will determine whether low-cost clinical tests can serve as markers to detect neuroinflammation as determined on MRI. The objective of the substudy is to determine whether the structural integrity of cutaneous nerve fibres is altered in the acute stage following a WAD2 injury, and whether it contributes to the progression to chronicity.

### Study design

This is a prospective cohort study at two centres. A total of 115 participants will be recruited following a whiplash injury within 1 month of their original injury. We will also recruit 34 healthy proportionally age-matched and gender-matched control participants. People with acute WAD2 and healthy control participants will attend a baseline appointment. In addition to MRI, a detailed musculoskeletal assessment will be performed, as well as tests of nerve trunk mechanical sensitivity and quantitative sensory testing (QST). A blood sample will be taken and analysed for levels of inflammatory markers. Participants will also be asked to complete a series of validated questionnaires to assess neuropathic symptoms, functional deficits, quality of life and psychological factors. For the substudy, skin biopsies from the index finger and ankle will also be taken. At 6 months, the Neck Disability Index and a self-rated global recovery question will be used to determine recovery. A sequential sample of patients will be invited to attend a follow-up appointment during which the same detailed assessments will be repeated (figure 1).

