### Participant recruitment

Patients aged 18–60 that meet the Quebec Task Force Classification of WAD2 will be recruited within 4 weeks of injury. Participants will be recruited from emergency departments and minor injury units in Surrey, Sussex, Kent and Oxfordshire, directly by clinicians, and following weekly hospital database searches using defined search terms (eg, motor vehicle collision, muscle injury: neck, bruise/contusion/abrasion: neck, sprain/ligament injury: cervical spine). Potential participants will be contacted in person, or by phone, and asked for permission for their details to be passed on to the study team, and/or sent the study details. In addition, posters will be displayed in departments with study contact details. Healthy age-matched and gender-matched control participants will be recruited through departmental emailing lists (Universities of Sussex and Oxford as well as local hospitals), social media and flyers on public notice boards. Potential participants will be screened for suitability via telephone and also be invited to take part in the substudy. Eligible individuals will be sent a participant information sheet and questionnaires to complete (please see table 1 and questionnaire section below) and will be invited to attend a baseline appointment at either Brighton and Sussex Medical School, University of Sussex, Falmer or the Nuffield Department of Clinical Neurosciences, University of Oxford.

**Table 1 T1:** Summary of self-reported and physical assessments

Test	Description	Type of tool/assessment	Participants
Demographics	Age, gender, height/weight.	Self-reported.	HC and whiplash
Injury details	Impact, anticipation.	Self-reported.	Whiplash
Medication details	Specific to WAD symptoms.	Self-reported.	Whiplash
Symptom history	Description of pain or symptoms.	Self-reported.	Whiplash
Pain level	Current pain severity.	Visual Analogue Scale.	Whiplash
Management	Any investigations/treatment.	Self-reported.	Whiplash
Type of pain	Neuropathic pain.	painDETECT Questionnaire.	Whiplash
Disability	Neck disability.	Neck Disability Index.	Whiplash
Psychological factors	Post-traumatic stress. Pain catastrophising. Depression, anxiety and stress. Quality of life.	PTSD-8. Pain Catastrophising Scale. DASS 42. EQ-5D-5L.	Whiplash

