#### Questionnaires

Patients will complete the following validated questionnaires: Neck Disability Index (NDI),^31 32^ pain detect questionnaire (painDETECT),^33^ short post-traumatic stress inventory (PTSD-8),^34^ Pain Catastrophising Scale (PCS),^35^ Depression, Anxiety and Stress Scale (DASS42),^36^ the quality of life questionnaire (EQ-5D-5L),^37^ and the Impact of Events Scale (IES-Revised).^38^

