### Statistical analysis

Data will be exported to Stata (V.17, StataCorp, Texas, USA) for analysis. The distribution of the data will be checked for normality, and parametric, or non-parametric methods will be used as appropriate. Participants’ characteristics will be described at all time points.

For objective 1, regression analysis, or non-parametric tests, will be used as appropriate to identify differences in MRI parameters (T2-weighted STIR 4 nerve roots per side, nerve morphology and DTI parameters) and clinical tests (eg, neuropathic pain scores, tests of nerve mechanosensitivity, QST and serum inflammatory markers) between participants with acute WAD2 and age/gender-matched controls. Regression analysis will be used to assess associations with age and height.

For objective 2, recovery of participants with WAD2 will be determined at 6 months with the Neck Disability Index and a global recovery question. The analysis will be conducted with three models using different predictors measured in the acute stage: (a) MRI parameters of neuroinflammation, (b) clinical parameters that reflect neuroinflammation and (c) the addition of MRI to clinical parameters to determine whether this improves predictive strength. The dependence between MRI and clinical assessments will be investigated and composite measures added to the model. In addition, a linear regression will be performed of Neck Disability Index scores on measures of neuroinflammation.

For objective 3, mixed effects modelling will be used to compare MRI and clinical measures between recovered and non-recovered participants with WAD2 over time.

For objective 4, multivariable regression will be used to investigate the relationship of each MRI variable with the clinical parameters of neuroinflammation. In addition, a regression analysis will be performed between clinical measures of neuroinflammation and MRI parameters.

For the substudy, independent t-tests or non-parametric alternatives will be used to compare dermal and intraepidermal nerve fibre density in skin biopsies in patients in the acute phase after whiplash injury with healthy controls. Separate regression models will be used to investigate whether changes in nerve fibre density in the acute stage predict pain persistence at 6 months.

Data reduction techniques (eg, principal components analysis) may be used prior to regression modelling.

Missing data will be managed with multiple imputation strategies.

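### The objective 2 models name no psychological score, so a positive clinical model (b) could reflect distress rather than neuroinflammation

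*Protocol article*

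**What the plan says.** The Study design section of the protocol article has participants "complete a series of validated questionnaires to assess neuropathic symptoms, functional deficits, quality of life and psychological factors". Table 1 lists the psychological domains for the whiplash group as "Post-traumatic stress. Pain catastrophising. Depression, anxiety and stress. Quality of life", measured with the PTSD-8, Pain Catastrophising Scale, DASS 42 and EQ-5D-5L. The Questionnaires section adds the revised Impact of Events Scale, which Table 1 does not list.

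For objective 2, the Statistical analysis section defines three models by their predictors. The first two use "a) MRI parameters of neuroinflammation, (b) clinical parameters that reflect neuroinflammation". The third model is described as "c) the addition of MRI to clinical parameters to determine whether this improves predictive strength". The section adds composite measures of MRI and clinical assessments, and a linear regression of NDI on measures of neuroinflammation. No psychological score is named there or elsewhere in that section.

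Recovery at 6 months is judged by the NDI and a self-rated global question (Study design). The Nerve mechanical sensitivity testing section scores the neurodynamic tests on the participant's own symptoms, the algometer on the participant saying when pressure turns to pain, and palpation on symptom response.

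**The concern.** In model (b), many predictors and both outcomes pass through the same channel, the patient's report. If a distressed patient tends both to report pain sooner on a nerve test and to report poorer recovery, the two will be associated even where nerve inflammation plays no part. Blinding the data analysis does not remove this, because the shared influence lies with the patient.

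The article labels this predictor set "b) clinical parameters that reflect neuroinflammation", and the study's main aim is the contribution of nerve pathology to WAD2 and to prognosis. A positive model (b) would naturally be read as evidence of mechanism. The data needed to examine the rival explanation are already collected, but the stated analysis does not use them.

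**Working it through.** **1. The plan's own figures.** With 8 assessments per participant, SD 0.1 and intraclass correlation 0.45, the SD of a participant's mean is 0.1 × √((1 + 7 × 0.45)/8) = 0.0720. Controls needed at 3:1, two-sided 5%, 80% power: (1.960 + 0.842)² × 0.0720² × (1 + 1/3) / 0.06² = 15.1, so 16 controls and 48 whiplash participants, as stated. Doubling for 50% chronicity gives 96 and 32, with 96 × 0.5 = 48 non-recovered. Five to ten predictors then have 48/5 = 9.6 to 48/10 = 4.8 events each. After 15% dropout, 115 × 0.85 = 97.75, or about 98 completers. These figures are not in dispute.

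**2. Assumptions for the size of the problem.** None of the following is in the documents: four clinical tests, each correlated r with distress and otherwise independent; distress correlated s with the latent recovery outcome; no neuroinflammation effect; 98 completers with 50% not recovered. The test is a 5% likelihood-ratio test of the four-test block in a logistic model, with and without a distress score of reliability 0.8.

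| r (distress-test) | s (distress-outcome) | Block significant, unadjusted | Adjusted |
|---|---|---|---|
| 0 | 0.3 | 6% | 6% |
| 0.2 | 0.2 | 8% | 6% |
| 0.2 | 0.3 | 10% | 7% |
| 0.3 | 0.3 | 16% | 7% |
| 0.3 | 0.4 | 25% | 6% |
| 0.4 | 0.4 | 37% | 8% |
| 0.5 | 0.4 | 47% | 8% |

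Repeat runs differ by a few points. The lowest setting gave 7-8%, the highest 47-52%, and adjusted rates reached 11%. With r = 0 the rate is about 5-7%, so that, not exactly 5%, is the floor for this test at this sample size. If the tests also correlate 0.3 with each other beyond distress, the unadjusted range for the settings from 0.3/0.3 to 0.5/0.4 is 12-36%, and the adjusted range 5-8%.

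**3. One clinical test alone.** With n = 96, r = 0.3-0.5 and an odds ratio for non-recovery of 1.5-2.5 per SD of distress, a test with no effect of its own shows an odds ratio of 1.13-1.51 per SD. It is significant in 8-45% of analyses, against 4-5% after adjustment for distress measured without error.

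**4. NDI regression.** For one clinical measure the induced correlation is r × s, and the rejection rate follows from atanh(r × s) × √93. At 0.3 × 0.3 = 0.09 this is 0.87, or 14%. At 0.5 × 0.4 = 0.20 it is 1.96, or 50%.

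**5. The MRI term in model (c).** An MRI term unrelated to distress and outcome, added to the four distress-related tests, was significant in 5-7% of runs. That is at the floor in step 2.

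**6. What adjustment can cost.** Suppose neuroinflammation truly acts and also raises distress (assumed loading 0.5-0.6 on tests and distress, direct effect 0.2-0.3, distress effect 0.3-0.4). Adjustment then cuts the power of the clinical block from roughly 40-85% to roughly 16-40%.

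**7. Predictor budget.** One extra term on top of 5-10 gives 48/6 = 8.0 to 48/11 = 4.4 events per predictor. Taken within the budget, the figures do not change.

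**The case against.** Several points on the other side stand.

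- **Silence is not exclusion.** A reader might infer that the plan rules psychological scores out. It does not: it never says the models are unadjusted, and a fuller analysis plan could add covariates. What stands is that the article defines the three models by predictor set, and none of the sets is psychological.
- **Objective 2 is partly pure prediction.** A prediction model needs no confounder adjustment. That is a reason to keep models (a) to (c). It does not cover attributing model (b) to neuroinflammation, as its label does.
- **Model (b) does not carry the claim alone.** The abstract ties nerve inflammation to MRI parameters, and objective 4 and the planned look at dependence between MRI and clinical assessments bear on whether the clinical tests track it. These checks help, but none of them adjusts for distress.
- **MRI results.** A reader might infer that models (a) and (c) give biased MRI findings. MRI is not a pain report and is analysed blind, and step 5 shows no inflation.
- **Not every clinical parameter is a pain report.** Serum markers are not, quantitative sensory testing includes detection thresholds, and a positive neurodynamic test also requires the symptoms to change with structural differentiation. Treating all four predictors as equally related to distress is a simplification.
- **The correlations are assumed.** The Introduction's remark, "Although a limited number of prognostic factors have been identified", does not say that those factors are psychological. At 0.1/0.3 the false-positive rate is only 7%.
- **Over-adjustment.** Distress is measured up to four weeks after injury and may partly result from nerve pain. Step 6 shows why a rule accepting model (b) only if it survives adjustment would often discard a true effect.

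**Conclusion.** The point holds for model (b), for the clinical terms in model (c) and for clinical measures in the NDI regression. As written, the analysis cannot separate neuroinflammation from distress as the reason the patient-reported nerve tests predict patient-reported recovery, although psychological scores are available to examine this.

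The size depends wholly on assumed correlations. With distress-test values of 0.2-0.5 and distress-outcome values of 0.2-0.4, a null model (b) is significant in about 7-50% of studies. After adjustment for one score of reliability 0.8 this is about 6-11%. If distress and the tests are unrelated there is no inflation. The documents do not support extending the point to MRI terms or serum markers, and do not support treating the unadjusted models as invalid for prediction.

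**What to change.** Keep models (a), (b) and (c) as the prediction models. Pre-specify a companion version of (b), (c) and the NDI regression that enters one baseline psychological score, for example the DASS-42 total or the first principal component of DASS-42, Pain Catastrophising Scale and PTSD-8. Count it within the 5-10 predictors. Report the clinical block with and without the score, and qualify any attribution of model (b) to neuroinflammation if the association disappears. Model (a) needs no such adjustment.

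The cost is a sentence or two of analysis wording, no new data, and one predictor of the budget. The statistical downside is possible over-adjustment, since distress after injury may partly result from nerve pain. Reporting both versions leaves that judgement open to the reader.

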**Figure 1 F1:**
[figure not shown]
Flow diagram showing the study design. WAD2, whiplash-associated disorder grade 2.

This study has been registered at ClinicalTrials.gov. The protocol version is V2 25 September 2020.

